### Neuropsychological Assessments

A set of neuropsychological tests will be used to assess cognitive function and behavior/mood of all the participants, and their activities of daily living will also be measured. The assessments will be performed at baseline, 12 weeks, and 24 weeks during the study period. (1) The Mini-Mental State Examination (Katzman et al., 1988) is the most frequently used assessment to measure global cognitive function. It is a 30-point scale that assesses orientation, memory, attention and calculation, recall, and language, with higher scores indicating better cognitive function. (2) The AD assessment scale-cognitive subscale (ADAS-cog; Chu et al., 2000) is a 12-item scale that primarily measures word recall, ability to follow commands, constructional praxis, naming, ideational praxis, orientation, word recognition, comprehension of spoken language, word-finding, language ability, and attention. The scores range from 0 to 75 and higher scores indicate greater cognitive impairment. (3) The Geriatric Depression Scale (GDS; Yesavage et al., 1982) is a short questionnaire to identify depression in older people and it is validated in mild to moderate dementia. (4) The Neuropsychiatric Inventory (NPI; Wang et al., 2012) is an assessment of 12 different behavioral and psychological symptoms common in AD. Each symptom is rated and scored according to the frequency and severity reported by the informants. The distress level of the caregivers associated with each symptom is also rated. (5) The Barthel Index (Mahoney and Barthel, 1965), is a 10-item, ordinal scale used to measure performance in activities of daily living. It is also performed by interviewing the caregivers.

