### Outcomes

The primary outcome will be the ADAS-cog score. The secondary outcomes will be the GDS and NPI scores. The safety of the RLT will be evaluated according to the incidence and severity of adverse events such as headache, dizziness, or nausea. The adverse events will be immediately reported, and handled by experienced physicians. Details of these possible adverse events and the treatments they receive will be recorded by filling in the case report forms. Physical examinations and necessary laboratory examinations, such as blood routine examination, liver function, and renal function, will be completed at baseline and the end of this study.

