### Sample Size Calculation

No studies have investigated the effects of RLT treatment on people with AD. However, there have been relevant published literature that reported positive effects of photobiomodulation (PBM) with 810 nm near-infrared light on people with dementia. For example, PBM was shown to reduce ADAS-cog scores by 6.73 points after a 12-week consecutive treatment (Saltmarche et al., 2017), and by 5.18 points in another report (Chao, 2019). In this study, we anticipate at least an effect size of 0.48 in ADAS-cog scores after 24-week RLT intervention. The sample size was calculated using Power Analysis and Sample Size software version 15.0 (NCSS, LLC)^1^. A total sample size of 48 participants is sufficient to detect the target effect size with 90% power (*β* = 0.10) and a type I error of 5% (*α* = 0.05). Considering a dropout rate of 10%, a total of 54 participants is necessary. In this study, we intend to recruit 60 participants, with 30 participants in each group.

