### Statistical Methods

Statistical analysis of demographics and clinical characteristics will be performed using IBM SPSS Statistics for Windows, Version 20.0 (Release 2011, IBM Corp, Armonk, NY, USA). Continuous data will be reported as means ± standard deviations or 95% confidence intervals, and as numbers with percentage for categorical data. The difference in demographic and baseline characteristics between two groups will be analyzed by using the independent *t*-test, and a *chi*-square test will be used for categorical variables.

The main analysis method for the safety and efficacy of RLT intervention in this study will use the intention-to-treat analysis including all randomized participants (Hollis and Campbell, 1999). Besides, a per-protocol analysis will be performed on individuals who complete the total study (Sedgwick, 2015). The repeated measures of variance analysis will be used to examine variations of scores of neuropsychological tests over time between two groups. The association between intervention and incidence of adverse events will be analyzed using the *chi*-square test.

fMRI data will be preprocessed by using Statistical Parametric Mapping version 12.0 (The Wellcome Trust Centre for Neuroimaging at UCL, London, UK) on the MATLAB platform (Release 2013b, The MathWorks Inc, Natick, MA, USA). There are several critical steps including motion correction, slice timing correction, spatial normalization, and smoothing. After fMRI data preprocessing, the fractional amplitude of low-frequency fluctuation and functional connectivity analysis will be analyzed by using the REST software version 1.8 (Song et al., 2011).

The level of significance for statistical analysis will be set at 5% (*P* < 0.05). The researchers who perform the data analysis will be blinded to the allocation and the intervention.

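### The stated ADAS-cog test is not tied to one 24-week between-arm estimate, although the trial is sized on an effect after 24 weeks

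*Protocol article*

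**What the plan says.** Four places in the protocol article bear on this.

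- Outcomes: "The primary outcome will be the ADAS-cog score". No visit is named, and neither change from baseline nor a between-arm difference is mentioned.
- Neuropsychological Assessments: "The assessments will be performed at baseline, 12 weeks, and 24 weeks during the study period". There are thus two post-baseline visits.
- Statistical Methods: a repeated measures ANOVA is to "examine variations of scores of neuropsychological tests over time between two groups". This is the only sentence on the efficacy test. It lists no levels of the time factor, no covariate, no tested effect and no contrast.
- Sample Size Calculation: "we anticipate at least an effect size of 0.48 in ADAS-cog scores after 24-week RLT intervention". The metric of the 0.48 is not given.

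**The concern.** The sample size looks to the end of treatment, but the test looks at the whole course. If baseline, 12 and 24 weeks are the three levels, the group-by-time interaction has 2 degrees of freedom and asks only whether the two mean profiles are parallel. It has no direction and no effect size, and it does not distinguish a difference at 12 weeks from one at 24.

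Two things are at stake. First, a significant result need not mean a benefit at the end of treatment, and several P values (interaction, 12 weeks, 24 weeks) could be read as the primary one. That matters more here because the Discussion acknowledges that there is no sham control. Second, baseline ADAS-cog is measured in everyone, and adjusting the week-24 comparison for it may be more precise at no cost.

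**Working it through.** **Step 1. The plan's own figure.** Inputs from Sample Size Calculation: effect size 0.48, 90% power, alpha 0.05 (two-sided assumed), total 48, dropout 10%. With (1.960 + 1.282)² = 10.507:

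| Reading of 0.48 | Normal approximation | Exact t |
|---|---|---|
| Between-arm Cohen's d | 2 × 10.507 / 0.48² = 91.2, so 92 per arm, 184 in total | 186 |
| Cohen's f, two groups (d = 2f = 0.96) | 2 × 10.507 / 0.96² = 22.8, so 23 per arm, 46 in total | 48 |
| Paired d | 10.507 / 0.48² = 45.6, so 46 | 48 |

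The stated 48 is reproduced as f or as a paired d, but not as a between-arm d. Dropout: 48 / 0.90 = 53.3, so 54, as stated. Because the metric is open, the steps below use both d = 0.48 and d = 0.96.

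**Step 2. Set-up.** Per arm n = 60 × 0.90 / 2 = 27. Assumed, not in the document: equal correlation r between all visits, equal variances, and the size of the 12-week effect.

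- Interaction: noncentral F with 2 and 2(2n − 2) = 104 df, critical value 3.084, noncentrality (n/2) × SS / (1 − r). SS is the sum of squared deviations of the three between-arm differences (in SD) from their mean.
- Week-24 ANCOVA: noncentral t with 2n − 3 = 51 df, critical value 2.008, noncentrality d × √(n/2) / √(1 − r²).

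**Step 3. Transient effect.** Differences (0, 0.48, 0) have mean 0.16 and SS = 2 × 0.16² + 0.32² = 0.1536.

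- r = 0.7: 13.5 × 0.1536 / 0.3 = 6.91, rejection probability 0.64.
- r = 0.8: 13.5 × 0.1536 / 0.2 = 10.37, rejection probability 0.82.

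The week-24 ANCOVA rejects at its nominal 5%, since there is no difference at that visit.

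**Step 4. Power for a week-24 effect of d = 0.48.** Half the effect at 12 weeks, (0, 0.24, 0.48), gives SS = 2 × 0.24² = 0.1152. The full effect at 12 weeks, (0, 0.48, 0.48), gives SS = 0.32² + 2 × 0.16² = 0.1536. For r = 0.7 and half effect, the noncentralities are 13.5 × 0.1152 / 0.3 = 5.18 for the interaction and 0.48 × √13.5 / √0.51 = 2.47 for ANCOVA.

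| r | Interaction, half effect at 12 weeks | Interaction, full effect at 12 weeks | Week-24 ANCOVA |
|---|---|---|---|
| 0.5 | 0.324 | 0.418 | 0.515 |
| 0.7 | 0.507 | 0.636 | 0.678 |
| 0.8 | 0.691 | 0.818 | 0.822 |
| 0.9 | 0.946 | 0.986 | 0.978 |

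The loss runs from 19 points (r = 0.5, half effect) to none (r = 0.9, full effect, where the interaction is slightly ahead).

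**Step 5. The same if 0.48 is f (d = 0.96).**

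| r | Interaction, half effect at 12 weeks | Interaction, full effect at 12 weeks | Week-24 ANCOVA |
|---|---|---|---|
| 0.5 | 0.886 | 0.958 | 0.979 |
| 0.7 | 0.986 | 0.998 | 0.998 |
| 0.8 | 0.999 | 1.000 | 1.000 |
| 0.9 | 1.000 | 1.000 | 1.000 |

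From r = 0.7 upwards the loss is about 1 point or less.

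**The case against.** The strongest reply is that the article is silent rather than wrong. Covariates and contrasts commonly sit in an analysis plan, which is not shown, and a repeated measures ANOVA is an accepted, unbiased comparison in a randomized trial. This stands as far as the handling of baseline goes: a reader might infer that the plan enters baseline as an outcome level and refuses it as a covariate, but neither is written. It does not cover the rest. The article itself fixes the test and the primary outcome, and nothing in it links either to the 24-week effect.

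Three further readings are tempting but unsupported.

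- That the plan wastes power outright. Steps 4 and 5 show that the loss depends on the correlation, the time course and the meaning of 0.48, none of which the article gives.
- That the test is the group main effect, which would average in a baseline difference of zero expectation and have low power. A sentence about variation over time between groups points to the interaction, so no weight is placed on the main effect here.
- That the test fails to estimate the effect on which the trial is sized. This cannot be shown, because that effect is never defined as a between-arm difference, a change or an f.

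**Conclusion.** The point holds as an ambiguity with a better method at hand. The primary outcome has no time point, and the only stated test is not tied to a 24-week between-arm estimate. The weakness in interpretation is the firmer part. It rests on reading the test as a three-level interaction and on equal correlation between visits, but not on what 0.48 means in the sample size: any transient 12-week difference of that order would often be declared significant. The power argument is secondary and conditional: 17 points at r = 0.7 and 13 points at r = 0.8 if d = 0.48 and half the effect is present at 12 weeks, shrinking to little or nothing under the other assumptions shown. The change should be made because it removes the ambiguity and uses only data already planned.

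**What to change.** Define the primary endpoint as ADAS-cog at 24 weeks. Make the primary analysis the between-arm difference at 24 weeks with its 95% confidence interval, adjusted for baseline ADAS-cog, either by ANCOVA or as the week-24 contrast of a mixed model with baseline as covariate. Make the 12-week contrast secondary. In Sample Size Calculation, state the 0.48 on that same between-arm scale, saying whether it is d or f, and confirm that 48 still follows. Use the same model for MMSE, GDS, NPI and the Barthel Index, each with its own baseline.

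The cost is rewording the outcome, analysis and sample size paragraphs, with no extra visits or data. If 0.48 proves to be a between-arm d, the stated 48 would not follow from an unadjusted comparison (Step 1), and the sample size would need to be recalculated.

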### Patient and Public Involvement

The original research question and outcome measures were conceived by the authors and were then modified based on face-to-face screening interviews with 16 elderly volunteers with cognitive impairment by a research assistant. They were also invited to use the RLT device for 3 months during the design phase of this study. The duration of treatment per time and frequency of treatment was determined based on their feedback to ensure the tolerance and the applicability of the intervention. These volunteers will not be included in this study. Both the potential burden and benefit of this study will be assessed by the participants and their guardians before signing the informed consent. The findings of this study will be made available to the participants and their guardians.

## Ethics and Dissemination

This study protocol has been approved by the ethical review committee of the Beijing Geriatric Hospital (approval number: 2019-024). Information leaflets of the study will be available at the public area of the Center for Cognitive disorders of BGH. The leaflets will explain in full detail the aims and objectives of the study, selection criteria, and the processes that the study will be adhering to. The research team will provide an individual face to face consultation to all potential participants and their guardians to answer any questions they may have before signing the consent form. Informed consent will be obtained from all participants and/or their legal representatives. Participants will be allowed to withdraw from the study at any time and the reason for withdrawal will be recorded. The results of this study will be reported in peer-reviewed journals and presented at national or international conferences on aging and dementia.

## Discussion

To our knowledge, this is the first RCT to investigate the safety and efficacy of RLT on AD. This 24-week study is designed to evaluate the effects of RLT intervention on cognitive function, mood, psychiatric and behavioral performances, and activities of daily living in older adults with mild to moderate AD. Also, neurophysiological changes assessed by fMRI and changes in blood/urine biomarkers associated with RLT will also be evaluated.

Preliminary evidence for the benefits of the RLT on AD has been obtained. The RLT can not only prevent early-stage memory decline but also rescue late-stage memory deficits in AD mice by reducing FA levels and oxidative stress (Zhang et al., 2019). Moreover, PBM with red to near-infrared light has been proposed as a non-invasive and innovative therapy for brain disorders. Some other beneficial effects of PBM have been reported, such as improved cerebral metabolic function (Oron et al., 2007; Rojas et al., 2012; Ferraresi et al., 2015), increased expression of neurotrophic factor expression, improved neurogenesis (Oron et al., 2006; Xuan et al., 2014, 2015), and reduced neuroinflammation (Lee et al., 2016; Aragona et al., 2017). Therefore, PBM appears to be a promising strategy for AD treatment.

There are limitations to this study. The first is that as the first preliminary clinical trial for the RLT device it is a single-center design. The second is the absence of a sham intervention for the control group for ethical and practical considerations. To minimize these shortcomings, the processes of randomization and blindness will be strictly carried out, and objective examinations including fMRI and blood/urine biomarkers will be conducted. Moreover, because of the cognitive impairments in patients with AD, the placebo effect can be greatly eliminated. The third is that follow-up assessment after cessation of the intervention is not planed in this protocol because the effects of the RLT are still unknown. If positive results are found in this initial study, future research will be conducted to assess the long-term influence of the RLT, which will help to identify the optimal RLT duration.

In summary, this RCT will explore the potential beneficial effects and safety of RLT on older adults with mild to moderate AD. The study will provide evidence for the clinical use of RLT on treatment for mild to moderate AD.

## Ethics Statement

The studies involving human participants were reviewed and approved by the Medical Ethics Committee of the Beijing Geriatric Hospital (approval number:2019-024). The patients/participants provided their written informed consent to participate in this study.
